## Abstract

**Background:**

The objective of the SCHLA-HF registry is to investigate the prevalence of sleep-disordered breathing (SDB) in patients with chronic heart failure with reduced left ventricular systolic function (HF-REF) and to determine predictors of SDB in such patients.

**Methods:**

Cardiologists in private practices and in hospitals in Germany are asked to document patients with HF-REF into the prospective SCHLA-HF registry if they meet predefined inclusion and exclusion criteria. Screening was started in October 2007 and enrolment was completed at the end of May 2013. After enrolment in the registry, patients are screened for SDB. SDB screening is mainly undertaken using the validated 2-channel ApneaLink™ device (nasal flow and pulse oximetry; ResMed Ltd., Sydney, Australia). Patients with a significant number of apneas and hypopneas per hour recording time (AHI ≥15/h) and/or clinical symptoms suspicious of SDB will be referred to a cooperating sleep clinic for an attended in-lab polysomnography with certified scoring where the definite diagnosis and, if applicable, the differentiation between obstructive and central sleep apnea will be made. Suggested treatment will be documented.

**Discussion:**

Registries play an important role in facilitating advances in the understanding and management of cardiovascular disease. The SCHLA-HF registry will provide consistent data on a large group of patients with HF-REF that will help to answer questions on the prevalence, risk factors, gender differences and stability of SDB in these patients by cross-sectional analyses. Further insight into the development of SDB will be gained by extension of the registry to include longitudinal data.

## Background

The prevalence of heart failure (HF) in western countries is about 1-2% of the adult population, with significant increases as age increases [1,2]. Recent guidelines differentiate between HF due to reduced systolic left ventricular ejection fraction (HF-REF) and HF with preserved ejection fraction (HF-PEF) and impaired diastolic function [3]. HF-REF is the most widely investigated and best understood type of HF [3], with a high prevalence in males with ischemic heart disease. In contrast, HF-PEF is more prevalent in women and often has a non-ischemic aetiology. Epidemiological data suggest that HF-REF and HF-PEF have a similar prognostic impact [4].

A number of co-morbidities have been linked to the development and progression of HF. One that is gaining increasing recognition is sleep-disordered breathing (SDB) with predominant obstructive (OSA) or central sleep apnea (CSA) with or without Cheyne-Stokes respiration (CSR). Small studies published to date have reported that the prevalence of SDB was almost 70-80% in patients with HF-PEF and up to 76% in those with HF-REF based on a cut-off of an apnea-hypopnea index (apneas and hypoponeas per hour of recording time; AHI) ≥ 5/h while moderate to severe sleep apnea with an AHI ≥ 15/h was prevalent in about half of the patients [5-7].

The Sleep Heart Health Study identified OSA as an independent risk factor for the development of HF [8], with more impact in men than in women [9]. Patients with CSA have been shown to have a reduced quality of life [10] and to be at increased risk of developing cardiac arrhythmias [11]. In addition, the prevalence of CSA-CSR appears to increase as the severity of HF increases and cardiac function decreases [5,6]. Thus, the occurrence of CSA-CSR and its severity is thought to mirror cardiac dysfunction [12,13]. In addition, SDB in general [14], as well as OSA [15] and, in particular, CSA [16,17] have been shown to be independently associated with worse prognosis in patients with HF-REF. Even when HF-REF patients are receiving optimal treatment of HF, including cardiac resynchronization therapy (CRT), even a low level of CSA-CSR or OSA appears to have a major impact on prognosis [18].

Patient registries are increasingly being recognized as an important source of data about the natural history of disease, the effects of interventions or treatments, the relationship between baseline variables and outcomes, and the impact of risk factors [19-21]. Registries can also generate hypotheses to be tested in future randomized controlled clinical trials [19] and can serve as screening instruments for randomized trials. In this paper, the SCHLA-HF registry is introduced, which was started to fulfil these needs simultaneously for SDB in HF. For example, enrolment into the SCHLA-HF registry is a requirement for patients to be recruited into the SERVE-HF study (‘Treatment of Predominant Central Sleep Apnea by Adaptive Servo Ventilation in Patients with Heart Failure’; NCT00733343) [22]. SERVE-HF is the first multinational, multicentre, randomised, parallel trial to assess the effects of the addition of adaptive servo-ventilation (ASV) to optimal medical management compared with medical management alone on prognosis in HF-REF patients with predominant CSA. Its major substudy (NCT01164592) [22] will investigate potential mechanisms of benefit (e.g. reverse remodelling effects using echocardiography or changes in sleep using PSG). As screening instrument, the SCHLA-HF registry will include thousands of patients with stable HF-REF.

The objective of the registry is to investigate the prevalence of SDB in chronic HF-REF patients as well as risk factors, gender differences and stability of SDB in such patients. This report details data collection and assessments that will be undertaken in patients prospectively included in the SCHLA-HF registry.

## Methods

The SCHLA-HF registry received central ethics approval from the Freiburger Ethikkomission for Germany. All aspects of the registry were conducted within the principles of Good Clinical Practice and in accordance with the Declaration of Helsinki.

### Design of the registry

All German sleep laboratories were invited to participate in the registry. However, the majority did not have the infrastructure necessary to run such a project. Sleep laboratories were then asked to contact cardiologists in their referral area to build networks between cardiology and sleep medicine, which allowed the registry and the SERVE-HF study to proceed. Participating cardiologists, who had been contacted by and were working with sleep laboratories, were asked to enroll consecutively all heart failure patients who fulfilled the registry inclusion criteria described below.

One hundred and thirty-eight centres in Germany (91 cardiology practices and 47 hospital cardiology departments) are testing patients with chronic HF-REF for eligibility (patient flow diagram, Figure 1). After enrolment in the registry, patients are screened for SDB. Patients with a significant number of apneas and hypopneas per hour recording time (AHI_screening_ ≥15/h) and/or clinical symptoms suspicious of SDB will be referred to one of the 66 cooperating sleep clinics for an attended in-lab polysomnography (PSG) with certified scoring where the definite diagnosis and will be made, and the suggested treatment will be documented (Figure 1). The registry was started in October 2007 and enrolment was completed at the end of May 2013. It is expected that data analysis will be complete by the end of 2014 and a final report available in 2015.

**Figure 1 F1:**
[figure not shown]
**Patient flow and populations in the SCHLA-HF registry.** AHI, apnea-hypopnea index; BMI, body mass index; LVEF, left ventricular ejection fraction; NYHA, New York Heart Association; PG, polygraphy; PSG, polysomnography; SDB, sleep-disordered breathing.

### Patients

For cardiologists screening patients, criteria for inclusion of patients in the SCHLA-HF registry are as follows: chronic HF diagnosed and treated according to the European Society of Cardiology (ESC) guidelines [23] ≥12 weeks prior to enrolment; moderate-to-severe left ventricular systolic dysfunction (left ventricular ejection fraction [LVEF] ≤45% by an imaging method such as echocardiography, radionuclide angiography, left ventriculography or cardiac magnetic resonance imaging) documented <12 weeks before enrolment; New York Heart Association (NYHA) class III or IV at the time of inclusion or NYHA class II with ≥1 hospitalisation for HF in the last 12 months; patient able to fully understand study information and give signed informed consent.

Patients are not eligible to be included in the registry if the had any of the following: current use of positive airway pressure (PAP) therapy; life expectancy <1 year for diseases unrelated to chronic HF-REF; cardiac surgery, percutaneous coronary intervention, myocardial infarction or unstable angina within 6 months prior to randomisation; CRT-implantation scheduled or performed within 6 months prior to randomisation; transient ischemic attack or stroke within 3 months prior to enrolment; primary hemodynamically-significant uncorrected valvular heart disease (obstructive or regurgitant) or any valvular disease expected to require surgery; acute myocarditis/pericarditis within 6 months prior to enrolment.

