### Assessments

#### Demographic and clinical data

Demographic data, information about severity of HF-REF (New York Heart Association functional class, NYHA) and aetiology of HF-REF are assessed. In addition, common comorbidities of HF-REF (atrial fibrillation and diabetes) and symptoms of HF-REF/SDB such as nocturia, nap time, nocturnal dyspnea as well as medication are documented. Documentation of LVEF measured by an imaging method such as echocardiography, radionuclide angiography, left ventriculography or cardiac magnetic resonance imaging within 12 weeks prior to enrolment was added when data collection was expanded in May 2009, after 2395 patients had been enrolled. Also, the documentation of diabetes and heart rhythm was added.

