#### Statistical analysis

All variables will be analyzed using descriptive statistics (frequency, mean ± standard deviation [SD], range or median ± interquartile range, whichever is appropriate). Student’s t-test will be used to compare mean values. A Chi-square test will be used to compare frequencies and proportions in two or more groups. Data will be used for a nested case–control study comparing patients with and without SDB (analysis population I) or patients with different severity and type of SDB (analysis populations II and III) with respect to their characteristics and history. Multivariate logistic regression modelling will be used to analyze the associations between suspected causes of SDB and the risk of developing that disorder taking the cluster structure of the data entered by the recruiting cardiologists into account. The models will include potential clinical predictors of SDB, or of the extent of SDB, that are assessed in the SchlaHF registry such as age, BMI, gender, LVEF, NYHA class, aetiology of HF, and atrial fibrillation. Models will be fitted by likelihood ratio-based stepwise backward variable selection. The predictive accuracy of the resulting models will be judged by cross validation. A p value of <0.05 is considered to be statistically significant. Statistical analysis will be performed with SPSS version 19.0 or higher (SPSS Inc., Chicago, USA) or STATA 12.0 or higher (StataCorp LP, College Station, Texas, USA).

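### The NYHA II versus III/IV association with SDB cannot be separated from recent HF hospitalisation, because the entry rule requires hospitalisation for class II only

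*Protocol article*

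**What the plan says.** The protocol article's Patients section sets no hospitalisation condition for NYHA class III or IV. The lower class enters only as "NYHA class II with ≥1 hospitalisation for HF in the last 12 months".

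Statistical analysis lists potential predictors of SDB for the logistic models, "such as age, BMI, gender, LVEF, NYHA class, aetiology of HF, and atrial fibrillation". It describes these models as relating presumed causes of SDB to the risk of the disorder. On fitting it says: "Models will be fitted by likelihood ratio-based stepwise backward variable selection". On significance: "A p value of <0.05 is considered to be statistically significant".

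Demographic and clinical data says that "information about severity of HF-REF (New York Heart Association functional class, NYHA) and aetiology of HF-REF are assessed". Recent HF hospitalisation is not among the variables listed there. Documentation of LVEF, the other severity measure in the predictor list, "was added when data collection was expanded in May 2009, after 2395 patients had been enrolled".

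Background reports that "the prevalence of CSA-CSR appears to increase as the severity of HF increases and cardiac function decreases", and the Discussion links worsening heart failure to more frequent and more severe SDB. The Limitations section discusses the multi-step procedure, the collaboration between cardiologists and sleep laboratories, and missing polysomnography. It does not mention selection by NYHA class.

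**The concern.** The entry rule depends on the exposure that will be analysed. All class II patients in the registry had an HF hospitalisation within a year, whereas class III/IV contains patients with and without one. Among patients without a hospitalisation there is no class II group at all, so no II versus III/IV comparison exists there.

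Determining predictors of SDB is a stated objective, and the wording about causes invites a risk-factor reading of each coefficient. If a recent hospitalisation marks a patient more likely to have SDB, class II has been enriched for SDB by selection and the gap to class III/IV shrinks. Backward elimination could then drop NYHA class, and the registry could report that functional class does not predict SDB when the entry rule produced that result.

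**Working it through.** The article gives no effect size, power or sample size calculation, so there is no stated figure to reproduce. Two steps apply.

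**Step 1: structure (no assumption needed).** Share with an HF hospitalisation in the last 12 months, from the Patients section:
- class II: 100%
- class III/IV: an unknown share *h*, between 0% and 100%

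Unless *h* is 100%, NYHA class and hospitalisation are associated in the registry by design. The rule treats III and IV alike, so it does not distort the contrast between them.

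**Step 2: possible size (every input assumed).**
- SDB prevalence in non-hospitalised class II: 40%, odds 0.40/0.60 = 0.667
- OR_N: true odds ratio, III/IV versus II, 1.0 to 2.0
- OR_H: odds ratio for hospitalisation given NYHA class, 0.8 to 2.0
- *h*: 0.3 to 0.7
- no interaction and no other covariates

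Formulas, with p = odds/(1 + odds):
- class II in the registry: odds = 0.667 × OR_H
- class III/IV in the registry: p = *h* × p(odds 0.667 × OR_N × OR_H) + (1 − *h*) × p(odds 0.667 × OR_N)
- registry OR = odds(class III/IV) / odds(class II)

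Worked case, OR_N = 1.5 and OR_H = 1.5:
- Class II odds are 0.667 × 1.5 = 1.0.
- Class III/IV: hospitalised odds 1.5, p = 0.60; not hospitalised odds 1.0, p = 0.50.
- *h* = 0.3: p = 0.3 × 0.60 + 0.7 × 0.50 = 0.53; OR = 0.53/0.47 = 1.13.
- *h* = 0.5: p = 0.55; OR = 0.55/0.45 = 1.22.
- *h* = 0.7: p = 0.57; OR = 0.57/0.43 = 1.33.

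Other cases:

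| True OR_N | OR_H | *h* = 0.3 | *h* = 0.5 | *h* = 0.7 |
|---|---|---|---|---|
| 1.5 | 0.8 | 1.75 | 1.68 | 1.60 |
| 1.5 | 1.0 | 1.50 | 1.50 | 1.50 |
| 1.5 | 1.2 | 1.32 | 1.37 | 1.42 |
| 1.5 | 1.5 | 1.13 | 1.22 | 1.33 |
| 1.5 | 2.0 | 0.92 | 1.05 | 1.21 |
| 1.2 | 1.5 | 0.90 | 0.98 | 1.06 |
| 1.2 | 2.0 | 0.74 | 0.85 | 0.97 |
| 2.0 | 2.0 | 1.21 | 1.39 | 1.60 |
| 1.0 | 1.5 | 0.75 | 0.82 | 0.89 |

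A baseline prevalence of 30% or 50% moves these results by about 0.02 at most. With OR_H above 1 and *h* below 100%, the registry OR always lies below the true one. With OR_H = 1 there is no bias, and with OR_H below 1 the bias runs upward.

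**Check of the remedy.** Among hospitalised patients only, the OR is (0.667 × OR_N × OR_H)/(0.667 × OR_H) = OR_N, so the assumed value is recovered exactly under the no-interaction model.

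**The case against.** A reader might infer that the entry rule demonstrably biases the NYHA effect to the null or reverses it. The documents do not support that. The direction requires hospitalisation to be positively associated with SDB given NYHA class and the other covariates. The Background sentence concerns central sleep apnea with Cheyne-Stokes respiration, whereas the screening outcome is any AHI of at least 15/h. The Discussion sentence is broader, but it gives no figure and says nothing about hospitalisation. Reversal appears only in part of the assumed range.

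Nor should one infer that class III/IV patients enter without a hospitalisation. They enter regardless of one, and those hospitalised both reduce the distortion and make a like-for-like comparison possible.

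Four further objections have weight:
- The odds ratios above are crude. The planned model adjusts for other covariates that could absorb part of a hospitalisation effect, although LVEF can do so only incompletely because it was not documented for the first 2395 patients.
- The predictor list is illustrative and the article condenses a fuller protocol. Hospitalisation had to be established to apply the class II criterion, and it may have been recorded for everyone. Its absence from the list is therefore not itself an error.
- Neither the coding of NYHA class nor its reference category is stated.
- For prediction among patients who meet the entry criteria, NYHA class remains a legitimate predictor.

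These points limit the claim about direction and size. They do not remove the structural one: class II in this registry is not class II heart failure in general, and the article interprets NYHA class as a candidate cause without saying so.

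**Conclusion.** The point holds in a limited form. As described, the II versus III/IV association cannot be separated from recent HF hospitalisation, and the Limitations section does not acknowledge this. That follows from the entry rule and the named predictors alone.

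Probable attenuation rests on a positive association between hospitalisation and SDB, which is plausible from the article but not quantified there. The range of about 1.1 to 1.3 for a true 1.5 is a crude illustration on assumed inputs, not an estimate for this registry. Reversal is possible only where a weak NYHA effect meets a strong hospitalisation effect.

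The consequence is confined to one named predictor, read as a functional-class effect or carried over to HF-REF patients at large.

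**What to change.** - **If HF hospitalisation in the last 12 months is recorded for class III/IV:** force it into every model that contains NYHA class, exempt from backward elimination, or report the II versus III/IV contrast among hospitalised patients.
- **If it is not recorded:** do not interpret the II versus III/IV coefficient, or its removal by backward selection, as evidence for or against an effect of functional class.
- **In either case:** label the group *NYHA II with recent HF hospitalisation* in tables and text, and add the selection to the limitations.

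The cost is one forced covariate or one restricted analysis, plus labelling. The NYHA conclusion becomes less precise and narrower, because it rests on hospitalised patients. Since enrolment closed in May 2013, a variable that was not captured would have to be collected retrospectively; the labelling and the restraint in interpretation need no new data. Confining functional-class conclusions to IV versus III would also avoid the problem, but it discards all class II data, and its precision cannot be judged because the text gives no counts by class. It is a trade-off rather than the default.

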### Assessments

#### Demographic and clinical data

Demographic data, information about severity of HF-REF (New York Heart Association functional class, NYHA) and aetiology of HF-REF are assessed. In addition, common comorbidities of HF-REF (atrial fibrillation and diabetes) and symptoms of HF-REF/SDB such as nocturia, nap time, nocturnal dyspnea as well as medication are documented. Documentation of LVEF measured by an imaging method such as echocardiography, radionuclide angiography, left ventriculography or cardiac magnetic resonance imaging within 12 weeks prior to enrolment was added when data collection was expanded in May 2009, after 2395 patients had been enrolled. Also, the documentation of diabetes and heart rhythm was added.

#### Screening for sleep-disordered breathing

After enrolment in the registry, SDB screening is then undertaken mainly using the two channel screening system ApneaLink™ (ResMed Ltd., Sydney, Australia) which measures nasal flow via a cannula and records pulse oximetry that has been validated in several studies for screening of SDB [24]–[29]. The default settings of the screening device were used for the definitions of apnea, hypopnea and desaturation: apnea was defined as an 80% decrease in airflow for ≥10 seconds; hypopnea was defined as a decrease in airflow by 50-80% versus baseline for ≥10 seconds; desaturation was defined as a ≥4% decrease in oxygen saturation; SDB in the screening process was defined as AHI_screening_ ≥ 15/h.

In addition, the ApneaLink™ provides a flow-based classifier as an automated diagnostic test for CSR. The classifier of ApneaLink uses various features for identifying CSR. The main features are the cycle length (for CSR usually 45–90 s), the apnea-hypopnea length, the hyperpnea length, and the shape of the hyperpnea as described previously [30]. Of the 138 cardiology centres, 15 used respiratory polygraphy for screening of SDB, either alone (n = 7) or in combination with ApneaLink™. Apneas and hypopneas were defined and scored according to the criteria above.

Patients with SDB or typical clinical symptoms are being referred to a sleep laboratory where a polysomnography (PSG) will be performed to make a definite diagnosis of SDB.

#### Diagnosis of obstructive or central sleep apnea with or without Cheyne-Stokes Respiration

PSG will contain brain activity (electro encephalogram, EEG), eye movement (electro oculogram, EOG), muscle activity or skeletal muscle activation (electro myogram, EMG), heart rhythm (electro cardiogram, ECG), breathing and respiratory effort measures during sleep as well as the recording of body position. Flow measurement has to be performed by nasal cannula and thermistor during diagnostic procedures.

A standardized qualification process for each center has been used to ensure comparability between centers in the scoring of respiratory events. Prior to participation every center had to send two diagnostic respiratory scorings to a central lab that validated whether such scorings were performed according to a detailed operating manual for technical requirements of PSG and respiratory scoring. If quality was not acceptable, specific training was provided, followed by another quality assessment. A key element of the PSG scoring manual is the differentiation of apneas and hypopneas as central or obstructive using flattening of the inspiratory airflow curve, paradoxical breathing, arousal position, sleep stages, and breathing pattern at the end of the hypopnea [31,32].

### Statistical considerations

#### Sample size

The sample size of the SCHLA-HF registry is linked to the recruitment period of the SERVE-HF trial. No formal sample size calculations were performed for the registry. A total of three prespecified analysis datasets have been defined (Figure 1): the “Screening Data Set” (“Analysis Population I”), the “PSG Data Set” (Analysis Population II) and the “PSG AHI ≥15 Data Set” (Analysis Population III). Numbers presented are those up to end of May 2013 (Figure 1).

